# Implementing a personalized pharmaceutical plan in kidney or liver transplant patients: study protocol for a stepped-wedge cluster randomized trial (GRePH)

**DOI:** 10.1186/s13063-021-05749-w

**Published:** 2021-11-08

**Keywords:** Personalized pharmaceutical plan, Therapeutic adherence, Immunosuppressive drugs, Clinical pharmacy, Community-hospital link, Transplantation, Medico-economic study, Stepped-wedge cluster randomized trial

## Abstract

**Background:**

Nowadays, the main challenge of transplantation is the improvement of long-term care, aiming at reducing treatment-related complications and at decreasing rejection rates. Patients’ adherence to both treatment and hygienic-dietary measures is mandatory to achieve these objectives. Adherence to immunosuppressive drugs is estimated to be only 70%. We hypothesized that the implementation of a personalized pharmaceutical plan (PPP) would increase adherence and therefore graft survival.

**Methods/design:**

This study is a stepped-wedge cluster randomized trial with transplantation units defining clusters. Twelve clusters from 10 university hospitals were recruited. All centres started on the same day in the control phase. Every 7 weeks, one centre will switch to the intervention phase and remain there until the end of inclusions. We plan to recruit 1716 kidney and/or liver transplant patients. The intervention phase consists in setting up the PPP: development of the patient’s hospital and community pharmaceutical follow-up. In the hospital, the pharmacist will carry out drug reconciliation upon admission, daily pharmaceutical follow-up of prescriptions and pharmaceutical interviews with the patient in order to explain the modalities of taking immunosuppressive drugs and hygienic-dietary measures. After hospitalization, during the post-transplantation year, pharmaceutical meetings will take place, prior to medical consultations in order to check the patient’s understanding of the prescription, his adherence, to remind them of hygienic-dietary measures and to look for adverse effects. The hospital pharmacist will also be in charge of establishing a close link with the community pharmacist (CP) and general practitioner, especially providing discharge medication reconciliation, an e-learning and a checklist. Moreover, prior to each pharmaceutical consultation, the hospital pharmacist will contact the CP to discuss patient adherence.

The primary outcome is adherence to immunosuppressive treatments 1 year post-transplantation assessed by using the BAASIS questionnaire and the health insurance data from the national health data system. A medico-economic study will measure the efficiency of this plan.

**Discussion:**

GRePH aims to increase adherence of liver and/or kidney transplant patients to their immunosuppressive therapies in order to reduce transplant rejections. To this end, a new clinical pharmacy model, the PPP, will be set up in 10 university hospitals.

**Trial registration:**

ClinicalTrials.gov NCT04295928. Registered on 5 March 2020

**Supplementary Information:**

The online version contains supplementary material available at 10.1186/s13063-021-05749-w.

## Background

In 2019, 6107 solid organ transplants were performed in France, with an annual increase of 1.6% and of 10% over 5 years. At the end of 2016, 22,617 patients were on the transplant waiting list. The two most concerned organs by transplantation were the kidney and liver with respectively 3641 and 1355 procedures performed [1]. Kidney transplantation (KT) is indicated for end-stage renal failure, especially in dialysis patients. Indications for liver transplantation (LT) are primarily acute or chronic hepatic failure and liver cancers. Kidney and liver transplantations allow patients to live almost normally, though they must take immunosuppressive drugs for the rest of their lives. In the last few years, progress has been made both in surgery and in immediate post-transplantation management. Therefore, the challenges of transplantation now lie in long-term transplant patient management, i.e. in the prevention of transplant organ rejection and of immunosuppressive drug side effects (cardiovascular diseases, cancers, infections). In fact, in 2017, graft survival rates at 5 and 10 years were respectively only 79 and 62% for KT and 69 and 58% for LT [2]. Moreover, the scarcity of grafts, in France, makes it necessary to maximize graft survival in order to reduce the rate of retransplantation [3]. This prevention of organ rejection requires optimum patient adherence to both drug treatment and dietary measures. Moreover, compliance with hygienic-dietary measures could partially limit adverse effects and also contribute to increase adherence.

In the literature, adherence of anti-rejection drugs is between 45 and 85% [4]. This variability could be explained by non-standardized evaluation methods from one study to another and to the absence of multi-centre evaluations [5]. In kidney transplant patients, non-adherence, in combination with other factors, is estimated to be responsible for 36% of rejections [6]. Among the risk factors for non-adherence, the lack of therapeutic education programme and the time to transplantation (with the spacing of consultations at the hospital) have been identified: over time, patients tend to be less adherent to their treatment.

We hypothesize that the combination of pharmaceutical follow-up during hospitalization and a better communication between health professionals is capital to patient adherence and therefore to graft and patient survival.

In 2017, the French Society of Clinical Pharmacy (SFPC) established a new model of clinical pharmacy [7]. This latter is based on the implementation of a personalized pharmaceutical plan (PPP) corresponding to management adapted to the patient’s pathway by proposing the best possible medication history, pharmaceutical interviews, pharmaceutical outpatient consultations and therapeutic education. These actions must be carried out both in hospital and in community pharmacy.

Post-transplantation follow-up is carried out by the transplant centre and, in some cases, according to local constraints, alternating by other centres closer to the patient’s home, but often quite far from the transplant team. There is little involvement of primary health care providers in the management of transplant patients. This is why the pharmacist, in collaboration with the transplant team, could be a relay to the patient ensuring continuity, repetition of messages and follow-up as soon as the post-transplantation consultations spread out. A reinforced community-hospital link between pharmaceutical professionals would help ensure continuity of care and optimized follow-up. Several studies have been conducted to improve patient adherence to treatment. With two exceptions, however, these studies remain monocentric and essentially concern only kidney transplant patients [8].

This protocol describes the GRePH study which aims to evaluate the impact of a PPP with usual practice on therapeutic adherence for immunosuppressive drugs in kidney or liver transplant patients who undergone transplantation in 10 French university hospitals (12 transplantation units).

## Methods/design

### Study design and randomization procedure

This study will be a stepped-wedge cluster randomized trial. Clusters will be 12 transplantation units. In cases where a hospital has both a kidney and liver transplant unit, these units will correspond to two clusters. However, if both kidney and liver transplant patients are managed within the same transplant unit, this latter unit will be considered as a single cluster. In a stepped-wedge trial, all centres start the study on the same day in the control phase. Then, one after the other, at regular time intervals, each cluster will switch to the intervention phase and remain there until the end of inclusions. During the control phase, the practices of the different centres will not be modified. During the intervention phase, the PPP will be deployed.

In order to gain power, there will be as many sequences (and therefore switch dates) as clusters, meaning that only one cluster at a time will switch from the control phase to the experimental phase. A 7-week transition period will take place at the beginning of all intervention phases, such that the intervention can be rolled out under optimal conditions. The clusters will all be randomized at the beginning of the study and cluster gatekeepers informed of the randomization result. Because some centres had to recruit staff to carry out the intervention phase, communication of the randomization result is mandatory. Randomization will be managed by the biostatistician of the study at the Clinical Investigation Centre (CIC) INSERM 1415. The patient recruitment period will last 23 months with a 3-year follow-up (Fig. 1).

**Fig. 1 Fig1:**
[figure not shown]
Schematic representation of the stepped-wedge study

### Clusters and participants

In total, this study will bring together 12 clusters (5 liver clusters, 6 kidney clusters and one mixed cluster) representing 10 French university hospitals (Brest, Marseille, Montpellier, Nantes, Poitiers, Strasbourg, Reims, Rennes, Toulouse and Tours).

Inclusion criteria are as follows: be 18 years old or older; have given their free, informed and express consent; speak French; live in France and have no plan to move for the duration of the study; declare going to the same community pharmacy each time (in France, 81% of French people declare themselves loyal to their community pharmacy [9]); and be health-insured.

Protected patients (safeguard of justice, curatorship or tutorship), already transplanted (whatever organ) or having benefited from a double transplantation (kidney/heart, kidney/liver with a centre not participating in the study or liver/heart) will be excluded.

### Recruitment and inclusion

Patients will be recruited postoperatively as soon as they will be able to understand the purpose of the research. Provided consent is given, all transplant patients meeting the inclusion criteria will be included in the study. The investigator of the centre will ensure the information and collection of the patient’s consent.

Patients are expected to be loyal to a community pharmacy. Consequently, any pharmacy may be involved in this present study. All community pharmacists (CP) will be informed of the study in three ways: a professional journal supported by the pharmacist union, a professional journal supported by the national council of the order of pharmacists and a letter sent by the study scientific committee distributed by wholesale drug distributors. CP having at least one patient included in this study will be informed of the study and the inclusion of their patient by hospital pharmacists. They will be given explanations on the study, how to use the tools and their key role.

### Sample size calculation

Currently, non-adherence to immunosuppressive treatment is approximately 30% [4]. The objective of the intervention is to reduce this percentage by one-third, i.e. to 20%. Considering a stepped-wedge design with 12 sequences (one cluster per sequence) of fourteen 7-week periods (one of which is a transition period), with a mean number of 11 patients recruited per cluster-period, this provides a 90% power to the study, taking into account an intraclass correlation coefficient of 0.01. Consequently, the total number of patients needed is 1716 of whom 132 are expected to be included in a transition period. Sample size calculation has been done using the shiny cluster randomized calculator [10, 11].

According to the French regulatory Agency’s 2017 data, the 12 recruited clusters could in turn recruit 2461 patients over 23 months. Considering that 25% of transplanted patients will have at least one exclusion criterion, 1846 patients will be included over 23 months.

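### The sample-size paragraph counts 1716 patients for a design that recruits 1848, and its 90% power falls to about 84% if transition-period patients are set aside

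*Protocol article*

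**What the plan says.** The Sample size calculation section takes non-adherence of about 30% under current care and aims for 20%. The design has "12 sequences (one cluster per sequence) of fourteen 7-week periods (one of which is a transition period"), and each cluster is expected to include 11 patients per period on average. From these inputs it concludes that "this provides a 90% power to the study, taking into account an intraclass correlation coefficient of 0.01", and that "the total number of patients needed is 1716 of whom 132 are expected to be included in a transition period". The abstract repeats the total as the recruitment target: "We plan to recruit 1716 kidney and/or liver transplant patients". Neither the significance level nor its sidedness is given.

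Three other sections bear on the point:

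- Study design and randomization procedure places a 7-week transition at the start of each cluster's intervention phase, so that the plan can be rolled out.
- Control and intervention phase places the pharmacists' training in the 7 weeks before the intervention phase. Trial status likewise lists a centre in transition separately from those in the intervention phase.
- Analysis says that all included patients enter the main analysis, in the group that matches their period of inclusion. It does not say which group the transition period belongs to.

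**The concern.** The total, the number of periods and the transition count cannot all be right as printed. The sample-size paragraph sets transition patients apart, which normally means they do not contribute to the treatment comparison. The power should then be that of a stepped wedge with one cell missing per cluster, at the point of the switch, where the design carries much of its information. If 90% was obtained without that gap, the type II error is understated, and readers, funder and ethics committee have a more favourable figure than the design delivers.

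**Working it through.** **Count.**

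- 12 clusters x 14 periods x 11 = 1848 recruited.
- Transition: 12 x 1 x 11 = 132.
- Outside transition: 1848 - 132 = 1716, which also equals 12 x 13 x 11.
- As printed: 1716 - 132 = 1584 = 12 x 12 x 11, i.e. twelve analysed periods, not thirteen.

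Fourteen periods agree with the calendar in Trial status: 7 October 2020 to 28 August 2022 is 690 days, or 98.6 weeks, against 14 x 7 = 98. So 1716 can be the non-transition count of the 14-period design, or the full count of a 13-period design. It cannot be a 14-period total that includes the 132.

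**Power: inputs.** From Sample size calculation: 30% and 20% (difference 0.10), intraclass correlation ρ = 0.01, m = 11 per cell, 12 sequences of one cluster. From Analysis: fixed period effects and one cluster random effect. Assumed: two-sided 5%. The individual variance σ² is (0.30 x 0.70 + 0.20 x 0.80)/2 = 0.185, or pooled 0.25 x 0.75 = 0.1875.

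**Formula.** For each cluster, the observed cell means have covariance V = σ²[ρJ + ((1 - ρ)/m)I], where J is all ones. With Z holding the period indicators and the treatment indicator, the variance of the treatment effect is the treatment element of (Σ Z'V⁻¹Z)⁻¹. Power = Φ(0.10/SE - 1.960). Cluster k is control in periods 1 to k. With a transition, period k+1 is dropped and the rest are intervention: 78 control, 78 intervention and 12 transition cells.

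**Results** (σ² = 0.185, then 0.1875):

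| Design, 11 per cell | Recruited | Analysed | SE | Power |
|---|---|---|---|---|
| 13 periods, no transition | 1716 | 1716 | 0.03099; 0.03120 | 89.7%; 89.3% |
| 14 periods, transition cells dropped | 1848 | 1716 | 0.03376; 0.03399 | 84.2%; 83.7% |
| 14 periods, transition cells analysed, correctly coded | 1848 | 1848 | 0.03074; 0.03095 | 90.2%; 89.8% |
| 13 periods including one dropped transition | 1716 | 1584 | 0.03407; 0.03429 | 83.5%; 83.0% |

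For example, in the second row 0.10/0.03376 = 2.962, 2.962 - 1.960 = 1.002 and Φ(1.002) = 0.842.

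The first row reproduces the plan's 90% and 1716 together. The second row analyses the same 1716 patients but with less information. Without a transition, only the first and last of 13 periods lack a concurrent control-intervention comparison; with the transition cells dropped, periods 1, 2, 13 and 14 all lack one.

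**Detectable difference at 90%, transition dropped.** (1.960 + 1.282) x 0.03376 = 0.109, and x 0.03399 = 0.110, so about 11 points. Keeping 10 points at 90% would take 13.75 to 14 patients per cell, i.e. 2310 to 2352 recruited (168 cells).

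**Sensitivity, transition dropped.**

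- Different variances in the two arms: 84.3%.
- Cluster autocorrelation of 0.8 to 0.9: 82.6% to 84.7%.
- One-sided 5%: 90.3% to 90.6%.

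**Sensitivity, transition analysed as intervention.**

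- Half the effect present in transition: expected estimate 8.4 points, power about 78%.
- No effect present in transition: expected estimate 6.9 points, power about 60%.

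**The case against.** The strongest reply is that the Analysis section excludes nobody. Read literally, transition patients are analysed, and since the design section puts the transition inside the intervention phase, they would be coded as intervention. The 14-period design then has 89.8% to 90.2% power, which is the stated figure. This stands in part: it is why the 84% must be given as conditional. But it needs the full effect during a roll-out period, or else no effect with those patients coded as control, and it needs 1848 analysed patients. The article is also not consistent on whether the transition lies inside or before the intervention phase, so the coding cannot be read off.

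A one-sided 5% test would also restore 90% with the transition dropped. Nothing in the article mentions one, and it leaves the count wrong.

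Four stronger readings are tempting but not supported:

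- *The calculation was certainly run on 13 periods without a transition.* That design reproduces both printed figures, but the calculator's inputs are not shown, and 1716 is equally 1848 - 132. The match suggests this without proving it.
- *The accrual of 1846 confirms 1848.* It is 2461 x 0.75, a forecast from national activity data that does not use the 11 per cell. It confirms nothing about the design total.
- *Inclusion will stop at 1716, leaving 81% to 82% power.* All eligible consenting patients are to be included over a fixed 23 months; no passage stops inclusion at a count.
- *The design simply has 84% power.* This holds only if transition patients are excluded, which the article does not state.

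**Conclusion.** The contradiction in the count holds under any assumption: the total is understated by 132, or the 132 is placed inside the wrong number, and the abstract carries the same figure. The power statement is wrong on the usual meaning of a transition period: about 84% (83.7% to 84.2%) rather than 90%, so a type II error of about 16% rather than 10%. That rests on two-sided 5%, an exchangeable cluster effect and exclusion of transition patients. About 90% is defensible at two-sided 5% only if those patients are analysed and correctly coded at full or no effect, which is optimistic for a roll-out period, and then the analysed number is 1848. No reading examined makes 1716 a 14-period total that includes the 132. The trial remains above 80% power with transition patients excluded, so this is a misstatement to correct and not a reason to doubt that the trial is worthwhile.

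**What to change.** In Sample size calculation, state the count as 12 x 14 x 11 = 1848 patients recruited, 132 in transition periods and 1716 outside them, and change the recruitment figure in the abstract to match. State alpha and its sidedness. Reconcile this section with Study design and with Analysis: say whether patients included during transition enter the primary analysis and, if so, in which group. Then give the power that goes with that choice (two-sided 5%): about 84% for 30% versus 20% if they are excluded, or equivalently 90% for about 11 points; about 90% only if they are analysed at full effect, with that assumption written down.

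The cost is rewording and possibly a less favourable stated power. No extra patients are needed: recruitment runs by calendar, and the plan's own forecast of 1846 is in line with 1848.

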### Control and intervention phase

The intervention flowchart is outlined in Fig. 2. During the control phase, patients included will be managed according to usual care. If educational and/or clinical pharmacy activities already exist in some clusters, they will be maintained with the collection of this information.

**Fig. 2 Fig2:**
[figure not shown]
Diagram showing the course of the study

During the intervention phase, the hospital pharmacist will be in charge of admission and discharge medication reconciliation, 3 pharmaceutical interviews, therapeutic follow-up and communication with the CP. Moreover, he/she will conduct 3 pharmaceutical consultations with the outpatient 1 month (M1), 3 months (M3) and 12 months (M12) after transplantation. To standardize this intervention over the various hospitals, hospital pharmacists will receive a 2-day training in medication reconciliation procedures, pharmaceutical interviews and consultations and therapeutic follow-up by an experienced clinical pharmacist who is accredited by the SFPC. Investigators (i.e. hospital pharmacist) from each centre will be trained at the sponsor centre (Tours University Hospital). Support documents (e-learning, support sheet for conducting pharmaceutical interviews, pharmaceutical consultations, drug reconciliations, standard letters to the attending physician, immunosuppressive drugs tryptic, checklist for CP, etc.) will be given to the trained centre. Each document will have been previously adapted to the current practices of the trained centre and validated by the latter. This training will take place in the 7 weeks preceding the intervention phase.

During hospitalization, the 3 pharmaceutical interviews will focus on anti-rejection drugs, adjuvant treatments to transplantation (anti-infectious chemoprophylaxis, antiviral, treatment of complications of immunosuppressive drugs: diabetes, hypertension, etc.) and hygienic-dietary measures. The first meeting allows the patient to be provided with a panel of simple information. The pharmacist will reformulate the information and explanations on request such that the patient memorizes the message. The second meeting will take the form of open questions. It will aim to assess what the patient has learned and understood. Do they know what time to take their treatments? Do they know what to do about meals? Do they know what precautions to take with regard to the sun? How to carry heavy loads? If necessary, the pharmacist will re-explain all these notions. The pharmacist can repeat this interview number 2 until the patient understands, memorizes, integrates and appropriates the information. In case of major difficulties or for non-autonomous patients, interviews may be conducted with a caregiver (by phone if needed). The third interview will take place on the day of discharge (or the day before if the discharge is scheduled), after a brief reminder of the instructions/information, an intake plan and a pill box for a nychthemeron will be issued to the patient. For each drug, the patient will have to explain in their own words its goal and moment to be taken relative to the time, other medications and/or meals. A report of each meeting will be placed in the patient’s file. These summaries will be available to the medical team in order to prepare the patient’s discharge: is the patient able to manage their treatment at home alone? In addition, they will be sent to the CP with the discharge reconciliation and prescription, thus strengthening the community-hospital link. The CP will thus be aware of the points of vigilance to be discussed with the patient. Discharge medication reconciliation and prescription will also be sent to the patient’s general practitioner (GP). These will specify the treatments initiated, modified or stopped following transplantation. Moreover, an e-learning on transplantation, the objectives to be achieved and patient management will be sent to the CP and GP. This e-learning will present a quiz for the various topics addressed, allowing the professional to check their knowledge. This e-learning will be personalized for each cluster to adapt to local specificities. Finally, a checklist with all information to be specified at the time of each dispensation will be sent to the CP by the hospital pharmacist.

At the time of the M1, M3 and M12 medical consultations, the hospital pharmacist will meet with the patient again. To further involve the patient, a booklet will be issued upon discharge from the hospital in order to inform them of the anticipated dates for the pharmaceutical consultations. For patients hospitalized at M1, M3 or M12, consultations will be staggered over time: they will be performed at the time of the first medical consultation following the patient’s discharge. The hospital pharmacist will carry out a drug assessment, draw up a list of undesirable effects, ensure appropriate drug intake, collect any problems or questions reported by the patient and will ensure the persistence of the educational messages given during the pharmaceutical hospitalization interviews. Also, prior to the consultation, he/she will contact the CP to ensure that this latter is in possession of the medication. A summary of this exchange will be written in the patient’s medical file and presented to the physician immediately prior to the consultation (Additional file 2).

Due to the nature of the assessed intervention, blinding will not be possible for patients and the healthcare team.

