### Outcomes

#### Primary outcome measure

The primary outcome is adherence to immunosuppressive treatments 1 year after transplantation (M12). To assess therapeutic adherence (compliance and persistence), a combination of two methods is recommended [12]. Accordingly, we will use the BAASIS (Basel Assessment of Adherence to Immunosuppressive Medication Scale) questionnaire and the health insurance data from the national health data system (SNDS). The BAASIS questionnaire [13] will be used 1 year after the transplantation (M12) (Additional file 3). This is a recognized questionnaire for assessing adherence to immunosuppressive therapy. It includes 4 questions to determine whether, in the last 4 weeks, the patient forgot to take, did not respect the taking schedule (to the nearest 2 h) or changed the dosage of their immunosuppressive treatment. A patient answering “yes” to one of the 4 questions will be treated as a non-adherent.

Using the SNDS health insurance data, we will verify that over the year following the transplantation, 100% of the days are covered by immunosuppressive drug possession by counting the number of tablets dispensed by the CP during this period (for hospitalization days, therapeutic adherence will be estimated at 100%). The SNDS health insurance data are described in Additional file 4.

To be considered as adherent, a patient must be assessed as an adherent on both criteria.

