### Data management

Health professionals with direct access will take all necessary precautions to ensure the confidentiality of information, particularly with regard to their identity and the results obtained. These persons, in the same way as the investigators themselves, are subject to professional secrecy.

For each patient who agrees to participate in the study, the investigator is provided with a follow-up notebook in which he records all the clinical and quality of life information required by the protocol. The investigator is responsible for the accuracy, quality and relevance of data entered. Each notebook is anonymised: data is coded with the first letter of the patient’s surname and first name and a number specific to the research (N1) corresponding to the order of inclusion of the patients.

A copy of these anonymised notebooks will be sent to the coordinating centre by secure mail. In the coordinating centre, a clinical research technician will enter data into the e-CRF.

Access to SNDS data requires patient identification data. After a favourable opinion from the CNIL, each investigating centre will transmit a table of identifying data to a trusted third party (independent of the coordinating investigator, the sponsor and the investigating centres) by a secure e-mail. This table will not contain any medical, pharmaceutical or paramedical data and will comply with a strict format standard. It will contain the patient code in the study (N1), the surname, the first name, the date of birth, the place of birth (postcode + town + country) and the sex. These data will make it possible to reconstitute the beneficiary’s SNDS identifier, used for extractions from the SNDS database. A new anonymous number (N2) will be created for each patient and the SNDS data will be transmitted by this new anonymous number to a secure project space. The trusted third party will send the patient number (N1)—anonymous number (N2) equivalence table to the Health-Economic Evaluation Unit (UEME) of the University Hospital of Tours. Then, the UEME will make the link between the clinical data collected specifically for the study and the SNDS data. The SNDS data will remain strictly on this project space, and no extraction will be performed.

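### The plan lets the M12 self-report outcomes be collected after the M12 pharmacist session, which only intervention patients have, and recorded by the pharmacist who delivers it

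*Protocol article*

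**What the plan says.** **The session.** Under Control and intervention phase, the hospital pharmacist's duties in the intervention phase include outpatient sessions: "he/she will conduct 3 pharmaceutical consultations with the outpatient 1 month (M1), 3 months (M3) and 12 months (M12) after transplantation". Their timing is tied to the medical visit: "At the time of the M1, M3 and M12 medical consultations, the hospital pharmacist will meet with the patient again". The Abstract (Methods/design) places these meetings before the medical consultations. It gives their purpose as checking understanding of the prescription and adherence, repeating the hygienic-dietary advice and looking for adverse effects. The later text adds that the pharmacist "will ensure the persistence of the educational messages given during the pharmaceutical hospitalization interviews". Control patients receive usual care. There is one timing exception: "For patients hospitalized at M1, M3 or M12, consultations will be staggered over time".

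**The outcomes.** Under Primary outcome measure: "The BAASIS questionnaire [13] will be used 1 year after the transplantation (M12"). Its recall window is short: "It includes 4 questions to determine whether, in the last 4 weeks, the patient forgot to take". A patient counts as adherent only if adherent on BAASIS and also fully covered by dispensed drug over the year in the SNDS data. Secondary outcome measures sets EvalOBS (last month) and a 9-item questionnaire on hygienic-dietary measures and how to take the immunosuppressants at M12 as well.

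**The recorder.** Control and intervention phase uses the terms interchangeably: "Investigators (i.e. hospital pharmacist) from each centre will be trained at the sponsor centre". Data management says that "the investigator is provided with a follow-up notebook in which he records all the clinical and quality of life information required by the protocol". Blinding of patients and care team is ruled out, and no separate assessor is named.

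**The concern.** One arm has a session at M12 that questions the patient about adherence and goes back over how to take the drugs. The other arm has none. The self-report outcomes are read at the same nominal time point, on overlapping topics. If the forms are filled in after the session, or handed to the person who ran it, the arms can differ for reasons unrelated to drug taking.

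The mechanism differs by instrument:
- **Knowledge score.** A session that repeats the messages can raise it directly. It would then measure recall over minutes rather than knowledge retained at one year.
- **BAASIS and EvalOBS.** The recall window has already closed, so the session cannot change the behaviour asked about. It can change what the patient is willing to report.
- **Primary composite.** A changed BAASIS answer alters the classification only if the patient also meets the SNDS criterion.

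Because the difference would coincide with arm, the planned mixed model with period and cluster effects could not separate it from a treatment effect.

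**Working it through.** **1. What is stated and what is inferred**

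| Element | Stated in the article | Left open |
|---|---|---|
| M12 pharmacist session | Intervention phase only, before the medical consultation | Nothing |
| BAASIS, EvalOBS, knowledge | Read at M12 | Same visit or not; before or after the session |
| Collector | Investigator records; investigator equated with hospital pharmacist | Who hands over and receives the forms |
| EQ-5D | Face-to-face at hospital visits preferred, otherwise phone | Order at M12 |

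EQ-5D is the only questionnaire with a stated collection mode, and that mode is tied to hospital visits. The only stated sequence puts the pharmacist first. So collection after the session is a natural way to follow the text, though the text does not require it.

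**2. The plan's own figure**

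Inputs from Sample size calculation: non-adherence 30% against 20%, 12 clusters, 11 patients per cluster-period, ICC 0.01, N = 1716, power 90%. Two-sided alpha of 0.05 is assumed, since none is given. Generalised least squares on cluster-period means (fixed periods, random cluster), mean variance (0.30 × 0.70 + 0.20 × 0.80)/2 = 0.185, 13 periods and no cells dropped (12 × 13 × 11 = 1716) gives SE 0.0310 and power Φ(0.10/0.0310 − 1.96) = 89.7%. The stated 90% is reproduced. With 14 periods and each cluster's transition period dropped, power is 84.2%. The present point does not depend on either figure.

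**3. Size of a reporting shift (illustration)**

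Let s be the share of the 30% non-adherent who fail BAASIS alone, and f the share of these who change their answers. The apparent gain in composite adherence with no true effect is

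shift = 0.30 × s × f.

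Neither s nor f is in the document. With s = 0.5 assumed:
- f = 0.10: 0.30 × 0.5 × 0.10 = 1.5 points
- f = 0.20: 0.30 × 0.5 × 0.20 = 3 points
- f = 0.33: 0.30 × 0.5 × 0.33 = 4.95, about 5 points

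With s = 1 (nobody fails on SNDS) these double to 3, 6 and 9.9 points. With s = 0 the shift is nil.

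**4. Effect on the test**

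With no true effect (variance 0.30 × 0.70 = 0.21), 14 periods and transition cells dropped, the SE is 0.036. The two-sided rejection rate is Φ(b/SE − 1.96) + Φ(−b/SE − 1.96):
- b = 0.015: 7.0%
- b = 0.03: 13.3%
- b = 0.05: 28.5%

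The nominal rate is 5%. With the 13-period design and no cells dropped (SE 0.033), the rates are 7.4%, 14.9% and 32.9%.

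**The case against.** The strongest reply is that the article is a condensation. The order of forms at a visit and the person who hands them out are working detail that may stand in the full protocol, Fig. 2 or the additional files, none of which is shown. That stands as a limit. If the order is already fixed there, the action reduces to confirming it in one sentence. It does not dispose of the point, because the article does give a sequence for the pharmacist and a recorder, and both point the wrong way.

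The link to the recorder is also indirect. It joins a remark about who is trained to a general data-management sentence. Recording is not administering, and if the pharmacist records for every patient, that role is the same in both arms. This is fair. What differs by arm is that intervention patients would answer to someone who has treated them for a year and may just have counselled them.

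A reader might go further and infer that the forms are certainly completed after the session with the pharmacist, that a knowledge difference is therefore almost certain, or that the whole planned effect could be a reporting artefact. The documents do not support this. Same visit, order and collector are inferences, and patients in hospital at M12 have the session deferred. The nine knowledge items are not shown, so only an overlap of topics is known. The last inference needs 0.70 + 0.30 × 0.33 = 0.80, with every non-adherent patient failing BAASIS alone and a third answering falsely. The documents give no basis for either figure, and the SNDS half of the endpoint is untouched by the session.

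**Conclusion.** The concern holds as a weakness in what the plan permits, not as a demonstrated bias. An intervention-only session shares its time point with the M12 self-report outcomes, nothing in the article stops those outcomes being collected after it, and the text points to the person who delivers it as recorder. Exposure is most direct for the knowledge score, provided it follows the session. It is indirect for EvalOBS and BAASIS, through answers only. It is partial for the primary composite, being confined to patients who meet the SNDS criterion.

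The size cannot be estimated from the document. The 1.5 to 5 point range rests on two assumed shares and shows only that a modest reporting shift would matter against a planned difference of 10 points. No planned analysis would remove the bias, so it has to be prevented at collection.

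**What to change.** State, identically for both arms, that at M12:
- Patients complete BAASIS, EvalOBS and the knowledge questionnaire themselves before any pharmaceutical or medical consultation.
- The completed forms go into a sealed envelope, sent with the notebook to the coordinating centre and entered by the technician who already enters the data there. The article documents no research staff at the sites, so the fix should not rely on any.
- If the M12 consultation is deferred because the patient is in hospital, the forms are still collected before it.
- EQ-5D keeps its planned mode (face-to-face preferred, phone otherwise), so that one of its six time points does not change mode, but it is collected before the session.

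Cost: a few minutes at the visit and slightly more incomplete items than with an interviewer. No added visit, and no change to any sample-size input. The change removes only the same-day effect. Social-desirability bias from a year of unblinded contact with the pharmacist remains and should be acknowledged as a limitation.
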